##### Cost and utility data

The medical data collected above will also be used for cost calculations. In addition, cost-utility will be measured through the European Quality of Life Scale (EuroQoL, EQ) [88]. The Spanish version of the 5-domain, 5-level EuroQol (EQ-5D-5L) [89, 90] will be used to calculate the QALYs. The EQ-5D-5L measures 5 domains of health-related quality of life (mobility, self-care, daily activities, pain/unease, and anxiety/depression) through 5 severity levels (*no problems*, *slight problems*, *moderate problems*, *severe problems*, and *extreme problems*). This makes it possible to establish up to 3125 different health states, each of which can be represented through an index value that reflects the health state quality contextualized in the person’s country/region. It also includes a visual analogue scale (VAS) that scores the respondent’s current subjective, general health state from 0 to 100. For more information, see van Reenen et al. [90].

#### Collection process

First, the 4-item PHQ ultra-brief subscale (PHQ-4) [91] will be used for the recruitment phase. The PHQ-4 gathers 2 items from the PHQ-2 and 2 from the GAD-2 (short versions of the PHQ-9 and GAD-7, respectively). It has been used in a Spanish primary care population (Spearman-Brown’s *ρ*_PHQ-4_ = .72; *ρ*_PHQ-2_ = .86; *ρ*_GAD-2_ = .76) [92]. A score greater than or equal to 3 would indicate the need for additional assessment (PHQ-2: a sensitivity of 90% and a specificity of 61%; GAD-2: a sensitivity of 88% and a specificity of 61%). It can be an extremely useful tool, as it helps to accelerate the screening process. It has been suggested, however, that both PHQ-2 and GAD-2 sum scores should be regarded separately in primary care samples [92]. The first item from the PHQ-PD has been added to screen panic disorder.

Second, depression, anxiety, panic, and somatizations will be assessed through the PHQ subscales mentioned above. If a participant scores as having a severe ED (depressive or anxiety disorder) or a non-emotional mental illness, or if the diagnosis is not clear, they will undergo a second evaluation with a gold-standard tool. The Structured Clinical Interview for DSM Axis-I Disorders (SCID-I) [93] will be used to assess panic and depression disorders and the Composite International Diagnostic Interview (CIDI) [94] will be used for GAD (since the former may not be adequate as it only includes one item for GAD). If these tools confirm the PHQ results, the patient will be referred to their GP, who will refer them to specialized care. The same will apply to those who score high in the SDS. All measures, except the PHQ-4, the SCID-I, the CIDI, and the treatment satisfaction question, will be collected at baseline, immediately after treatment, and 6 and 12 months later (see Table 2). Data will be also collected from medical records for the 3 months before participation in the study. To facilitate completion, the questionnaires may be answered in person, by email, online, or by phone.

To reduce the number of withdrawals, the clinical psychologists will telephone the participants to encourage them to continue with the treatment and/or to participate in the follow-up assessments. People who drop out of the intervention will still be invited to complete the questionnaires, especially at the first post-treatment assessment (immediately after the intervention).

### Data management

Scores from both electronic and paper questionnaires will be tabulated in SPSS Statistics. Data from the online instruments will be exported to SPSS.

### Statistical methods

#### Analysis of clinical effectiveness

Data analysis will be carried out using SPSS Statistics. Effectiveness-related data will be analysed using intention-to-treat and per-protocol approaches. After the homogeneity of intra- and inter-groups is checked, changes over time (baseline, post-intervention, and follow-ups) in primary and secondary outcomes will be analysed using linear mixed models (LMMs), since this method has been recommended rather than ANOVA or MANOVA analyses because LMMs do not require participants with missing values to be omitted nor imputed, and they are more adequate for repeated measures [95]. Likewise, effect sizes (Cohen’s *d* with bias corrections) will be calculated, as well as their accuracy (by taking into account the number of treatment sessions). The percentage of patients in each cluster who experience a 50% decrease in the number of clinical symptoms and scores to one standard deviation and the percentage of cases with a probable ED before and after receiving treatment (according to cut-off criteria) will be calculated. Therapeutic success criteria will be determined by obtaining post-intervention means significantly lower (*p* ≤ .05) and medium/large effect sizes significantly higher than those of the controls, especially in the ED scores. Clusters will be also compared regarding impairment, quality of life, emotion regulation biases, and satisfaction with treatment.

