### Sample size

We used effect sizes from the previous literature to determine the sample size. Corpas et al.’s primary care RCT [41] compared both group and individual brief tCBT with TAU for emotional disorders and found low to medium effect sizes for all outcomes. Individual effects were larger (Cohen’s *d* ranged from .54 to .74) than group effects (.4 to .63) when compared with TAU; however, there was no significant difference between both transdiagnostic formats, with (very) low effect sizes (.06 to .27). Another primary RCT by Corpas et al. [36] compared tCBT with TAU and found medium to large effect sizes (from .39 for depression to .81 for panic symptoms). Finally, the PsicAP study compared the group tCBT used herein to TAU in primary care. Intention-to-treat analyses showed low to medium effect sizes over time for depression (Morris’ *d* ranged from .36 to .58), anxiety (.38 to .65), and somatizations (.31 to .4). Subsequently, we decided to assume a medium effect size of .6 (Cohen’s *d*).

Since software to determine sample sizes for linear mixed model analyses was not available, we used the *f* index of G*Power [52]. We assumed an effect size of .3 (the equivalent *f* value); a statistical power (1 - *β*) of .8; and a significance level (*α*) of .05, obtaining a required sample size of 111. However, to control withdrawals and take into account the abandonment rates in other similar trials [36, 41], we assumed a dropout rate of 15%, which brought the required sample size to 128.

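### Success is worded on post-intervention means, and neither contrast offered by the planned mixed model conditions on the baseline score, which loses precision and lets chance baseline gaps carry over

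*Protocol article*

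**What the plan says.** The Analysis of clinical effectiveness section sets an order: "After the homogeneity of intra- and inter-groups is checked, changes over time (baseline, post-intervention, and follow-ups) in primary and secondary outcomes will be analysed" by linear mixed models. The homogeneity check has no named test or threshold and no stated consequence. The Outcomes section likewise says that effectiveness is judged on change from pre-treatment to the later visits.

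The success rule follows in the same section: "Therapeutic success criteria will be determined by obtaining post-intervention means significantly lower" than those of the controls at p ≤ .05, together with medium or large effect sizes. It does not say whether these means are adjusted, or which model contrast yields them.

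Under Collection process, the measures "will be collected at baseline, immediately after treatment, and 6 and 12 months later". The exceptions are the brief screener, the two diagnostic interviews and the satisfaction question. Every outcome scale therefore has a baseline value.

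**The concern.** Two different contrasts are in play. The model is described in terms of change over time, while success is worded in terms of level after treatment. Neither is the contrast that makes best use of a baseline measurement in a randomised trial.

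If success is read from the difference at the post-treatment visit, an arm that happened to start lower keeps part of that head start. If it is read from the group-by-time term, the whole baseline gap is subtracted. This over-corrects unless the baseline-outcome correlation is 1, and it adds noise when the correlation is modest.

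A homogeneity check does not repair either reading. Under randomisation any baseline difference is due to chance, and at this sample size a significance test passes gaps large enough to matter. At stake are precision in the therapy-versus-TAU comparisons and the credibility of a result obtained when the arms did not start level.

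**Working it through.** **Inputs from the Sample size section.** The article gives "a significance level (*α*) of .05, obtaining a required sample size of 111". The target power behind that total is 80%, and the effect entered is f = .3, matched to an assumed d of .6. For attrition it says: "we assumed a dropout rate of 15%, which brought the required sample size to 128". Trial design gives three arms, 1:1:1.

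**The plan's own figure.** For a three-group one-way F test with noncentrality f²N = 0.09 × N, power is 0.792 at N = 108 and 0.803 at N = 111. N = 111 is the smallest total reaching .80, so it reproduces. Per arm this is 111/3 = 37. The inflated total gives 128/3 ≈ 43.

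**Assumptions not in the document.** Baseline-outcome correlation r = .3, .5, .7; equal SDs; pairwise two-sided tests at 5%; and, for the homogeneity check, a pairwise t-test at 5%.

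**What the model contrasts estimate.** Let g be the observed baseline gap in SD units. With free arm means at every visit and complete data:

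| Contrast | Variance relative to post mean | Carry-over of g |
|---|---|---|
| Difference at post visit | 1 | r·g |
| Group-by-time (change) | 2(1 − r) | −(1 − r)·g |
| Baseline-adjusted | 1 − r² | 0 on average |

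**Power for d = .6 at 37 per arm.** The noncentrality for the post mean is .6 × √(37/2) = 2.58 on 72 df. For the other two contrasts, divide by the square root of the variance factor.

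| r | Post mean | Change score | Baseline-adjusted |
|---|---|---|---|
| .3 | 72% | 58% | 76% |
| .5 | 72% | 72% | 84% |
| .7 | 72% | 91% | 95% |

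**Which gaps pass the check.** The smallest observed gap significant at 5% is t_crit × √(2/n). At 37 per arm this is 1.993 × √(2/37) = 0.46 SD, and at 43 per arm it is 0.43 SD.

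**How often such gaps arise.** At 37 per arm the SE of the gap is √(2/37) = 0.2325 SD. A gap of 0.30 SD is z = 1.29 (two-sided probability about 19.7%), and 0.46 SD is z = 1.99 (about 4.6%). The chance of a gap between them is about 15% for a given scale and pair of arms.

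**What an unflagged gap does to an unadjusted post-visit comparison with no treatment effect.**
- Suppose therapy starts 0.4 SD lower at 37 per arm. The post difference then has mean r × 0.4 and SE √(2(1 − r²)/37), against a critical value of 0.463. At r = .5 the mean is 0.20 and the SE 0.201, so (0.463 − 0.20)/0.201 = 1.31. The chance of a false finding in favour of therapy is 9.5%, against a nominal 2.5%. At r = .7 it is 13.5%.
- In a null simulation of 200,000 runs at 43 per arm, the two-sided error among runs with a gap of 0.30–0.45 SD in either direction was about 0.10 (r = .5) and 0.14 (r = .7). Over all runs it was 0.05.

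**The case against.** The strongest reply is that a journal article need not specify the model. Whether baseline enters as a covariate, as constrained means or through change is commonly left to the full protocol or analysis plan. The success clause does not call its means raw. The homogeneity check is given no gatekeeping role, and its mention of within-group homogeneity may point to variances rather than to a comparison of baseline means. Change from baseline is a valid, unbiased analysis under randomisation, and at r = .7 it comes close to the adjusted analysis (91% against 95%).

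Much of this stands. That the means are unadjusted is an inference from the wording. A reader might also infer that the trial's false-positive rate is inflated, but the simulation shows 5% overall. The higher rates apply only given a baseline gap of a certain size. The check's form, and hence the 0.46-SD limit, is assumed.

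What the reply does not remove is that the article does fix a success rule. That rule is stated on post-intervention level, differs from the change-over-time analysis in the same section, and mentions no baseline adjustment. On either available reading, the contrast is less precise than one that conditions on the baseline score.

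**Conclusion.** The point holds as one of precision and conditional bias, not of overall validity. At 37 per arm and d = .6, baseline adjustment raises pairwise power over post means from 72% to 76%, 84% or 95% at r = .3, .5 or .7. Over change scores the gain runs from 18 percentage points at r = .3 (76 − 58) to 4 at r = .7 (95 − 91). The correlations are assumed. The pairwise power is a yardstick for comparing contrasts; the plan's 80% refers to the three-arm F test, which reproduces.

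Two stronger readings are tempting and are not supported:

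- A reader might infer that the baseline scores go unused. The Outcomes and Analysis of clinical effectiveness sections both place baseline in the analysis as a time point. What is missing is conditioning on it in the success contrast.
- A reader might infer that the homogeneity check overlooks a 0.5-SD imbalance about 40% of the time. A pairwise 5% test does have a type II error of 43.6% at 37 per arm and 37.0% at 43 for a true population gap of that size, but randomisation rules out a true gap. An observed 0.5-SD gap would be significant (p = .035 and p = .023), and a chance gap larger than that has a probability of only 3.2% or 2.0%. The gaps that pass and still matter are those of roughly 0.30–0.46 SD.

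**What to change.** Define the success contrast as the therapy-minus-TAU difference at post-treatment, 6 months and 12 months from a linear mixed model that adjusts for the baseline value of the same scale. Either enter baseline as a covariate, or keep it as an outcome with arm means constrained equal at that visit. Name one of the two in advance.

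In the success rule, say that the post-intervention means compared are baseline-adjusted. Apply the adjustment whatever the homogeneity check shows, and report baseline values by arm descriptively. The satisfaction question has no baseline value and stays unadjusted.

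The cost is a change of wording in the statistical section, made before outcome data are analysed by arm. The baseline scores are already scheduled, and the mixed-model procedure in the planned software fits either form.

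### The success rule (p ≤ .05 plus a medium/large effect size) is not the test the sample size powers: one format vs TAU has about 72% power on significance alone, and less if an effect-size floor binds

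*Protocol article*

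**What the plan says.** The protocol article, under *Analysis of clinical effectiveness*, defines therapeutic success by two conditions joined by *and*. Post-intervention means must be significantly lower at p ≤ .05, and there must be "medium/large effect sizes significantly higher than those of the controls, especially in the ED scores". Effect sizes are to be Cohen's d with bias correction. The section gives no number for *medium*. It also does not say whether the effect size is a between-arm difference or each arm's own change set against the controls' change.

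Under *Sample size*, the authors review earlier trials and state: "we decided to assume a medium effect size of .6". They convert this to f = .3 and enter it in G*Power with "a statistical power (1 - *β*) of .8" and "a significance level (*α*) of .05", "obtaining a required sample size of 111". An allowance of 15% for dropout brings the total to 128. The effect-size half of the success rule is not mentioned there. The same section describes an earlier trial as showing "medium to large effect sizes (from .39 for depression to .81 for panic symptoms", so *medium* covers both .6 and a range that starts at .39.

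**The concern.** A power statement should describe the chance of meeting the rule by which the trial will be judged. Here the rule has a second hurdle that the calculation leaves out. When an estimate must reach a size close to the assumed true effect, it often fails through sampling error alone. A format that works as planned and is significantly better than TAU could then be recorded as not successful.

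Because *medium* has no stated lower limit, a significant result with an observed d of .47 would pass under one reading and fail under another. The reading could be chosen after the data are seen. Borderline results are likely: the sample size section reports earlier group-versus-TAU effects of .4 to .63.

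**Working it through.** **1. Reproduce the plan's figure.** Inputs from *Sample size*: f = .3, α = .05, power .8. Three arms at 1:1:1 come from *Trial design*. For a one-way omnibus F test with N = 111, the degrees of freedom are 2 and 108 and the non-centrality is N·f² = 111 × .09 = 9.99. Power is .803. The next smaller balanced size, 108, gives .792. So 111 is the three-group omnibus test, with no effect-size condition.

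**2. Power for one format against TAU, significance only.** With n = 111/3 = 37 per arm and true d = .6, df = 72 and the non-centrality is d·√(n/2) = .6 × √18.5 = 2.581. The two-sided critical value is t = 1.993 (sidedness is not stated; two-sided is assumed). Power is P(t ≥ 1.993) = 72.1%. No effect-size condition has entered yet.

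**3. Add a floor on the observed between-arm d.** The bias-corrected estimate is g = t·√(2/n)·J, with J = 1 − 3/(4·72 − 1) = .9895. The smallest significant g is 1.993 × √(2/37) × .9895 = .459. Success requires t to exceed the larger of 1.993 and floor·√(n/2)/J. The floors are assumptions: .39 and .6 are values the protocol labels, and .5 lies between them.

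| Floor on g | t needed | Chance of success |
|---|---|---|
| .39 | 1.993 (floor not binding) | 72.1% |
| .5 | 2.173 | 65.9% |
| .6 | 2.608 | 49.3% |

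**4. Vary the number analysed.** 128 less 15% is 108.8, about 36 per arm: 70.9% on significance alone, 65.6% with floor .5 and 49.3% with floor .6. With no dropout, 128/3 = 42.7 per arm: 78.2%, 67.0% and 49.3%.

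**5. Allow for baseline adjustment.** The protocol gives no pre-post correlation. With an assumed correlation of .3 to .7 and a normal approximation at 37 per arm, significance alone has 77% to 95% power. Adding the floor gives 67% to 73% (floor .5) or 50% (floor .6).

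**6. The alternative reading: each arm's own pre-post effect.** Simulation with 37 per arm, between-arm d = .6, pre-post correlation .3 to .7, p ≤ .05 for the between-arm difference, and g ≥ .5 for the therapy arm's own change. TAU's improvement is an assumption.

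| TAU improves by | Chance of success |
|---|---|
| 0 SD | 54% to 57% |
| .2 SD | 69% to 71% |
| .3 SD | 71% to 72% |
| .5 SD | no loss (72%) |

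**7. Does sample size help?** With true d = .6 and floor .5, the chance rises with n: 65.9% at 37 per arm, 75.4% at 100 and 83.6% at 200. When the floor equals the true effect it stays near one half. For example, with both at .5 and 200 per arm, significance alone gives 99.9% but the joint rule gives 49.8%.

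**The case against.** The strongest objection is that a reader might infer that the effect-size condition alone pulls the power from 80% to 66%. It does not. The 80% belongs to an omnibus test. Moving to one format against TAU costs about 8 points (80% to 72%), and a floor of .5 costs about 6 more. A floor of .39, which the protocol's own wording allows, costs nothing. Calling .6 a medium effect does not make .6 the lower limit of medium, so 49% is one end of a range and not the plan's implied figure.

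The phrase about exceeding the controls' effect sizes can also mean that every arm has its own effect size. *Objectives and hypotheses* supports this, since it speaks of effect sizes per treatment, TAU included. The between-arm floors would then not apply, and the loss is small once TAU improves by .2 SD or more.

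Nor does a single probability follow from the rule, which is tied to neither one outcome nor one format. With floor .5 at 37 per arm, at least one format succeeds in 81% of simulated trials and both succeed in 51%. Hypothesis 2, however, expects TAU to be least effective, which concerns both formats.

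Finally, asking for a worthwhile effect as well as a small p-value is a defensible aim, and the cost-effectiveness and cost-utility ratios do not depend on this label.

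All of this limits the size of the point. It does not supply a calculation for the rule as written, and the competing readings show that the rule is not fixed.

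**Conclusion.** The point holds in a limited form. The success rule is not the rule that was powered. For one format against TAU at 37 per arm, with true d = .6, two-sided .05 and no baseline adjustment, the chance of success is below the stated 80% on every reading examined. It is 72% on significance alone; 72%, 66% or 49% with a between-arm floor of .39, .5 or .6; and about 54% to 72% if the effect size is each arm's own pre-post change with a floor of .5.

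Two limits apply. Baseline adjustment with a large enough assumed correlation lifts significance alone above 80%, though not the joint rule at a floor of .5 or .6. A reader might also infer that more patients can never repair the rule. That is true only when the floor equals the true effect; at the planned .6 with a floor of .5, a larger trial does help, though slowly.

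**What to change.** Under *Analysis of clinical effectiveness*, define success by the mixed-model difference of each format from TAU, with its p-value and 95% CI. Report Cohen's d with its 95% CI as a description of size and remove it as a condition. Under *Sample size*, restate the power for that pairwise contrast: about 72% at 37 per arm without baseline adjustment, or another figure if a pre-post correlation is stated and justified.

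If the sponsor prefers to keep both conditions, the text should name the effect-size contrast (between arms or within arm), fix one numerical lower limit for *medium*, and give the power of the full rule.

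Either route changes a few sentences and needs no extra patients or data. The cost is a less favourable stated power.

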#### Cost analysis

Cost-related data will be collected through medical records and ad hoc questionnaires, from 3 months before inclusion in the study to 12 months after the intervention. Direct costs will be calculated by adding the ED-related costs due to medication use (antidepressants, anxiolytics, hypnotics, and sedatives), medical tests and other health services, and health personnel (primary/specialized care and public/private care). Medication costs will be calculated by multiplying price per milligram (€/mg) according to the Vademecum International (including VAT) [96] by the daily dose (mg) and the number of days of drug treatment. Cost data relating to medical tests and the use of health services will be obtained through the fee information published on the Andalusian Health Service’s official website [97]. Since a group psychotherapy session does not have a specific tariff, it will be considered as a GP consultation without medical tests because GPs and clinical psychologists have similar basic salaries [98]. Indirect costs will be calculated by multiplying the days of ED-related sick leave by the participant’s current daily minimum salary; the expense of replacement workers will also be factored in when incurred. Total costs will be obtained by summing direct and indirect costs.

#### Analyses of cost-effectiveness and cost-utility

Cost-effectiveness analysis will be conducted by calculating incremental cost-effectiveness ratios (ICERs), which are defined as the difference in mean costs between interventions divided by the difference in their effectiveness according to the participants’ mean scores (i.e., one ICER per each comparison between two clusters and per each instrument). However, cost-effectiveness analyses are open to question since they rate the more appropriate intervention based only on the clinical perspective. Cost-utility analyses use the intervention health-related utilities, subjectively rated by participants. Therefore, they depend on a social perspective, that is, the participants express their preferences based on the value they assign to their health status. The EQ-5D-5L will be used to calculate those utilities as QALYs, and the latter will be used to obtain the incremental cost-utility ratios (ICURs), defined as the difference in mean costs divided by the difference in mean QALYs (i.e., one ICUR per each comparison between two clusters). Since follow-ups will not go beyond 12 months post-intervention, neither costs nor results will be subject to discount. The bootstrapping method (a resampling method) will be used to obtain more accurate ICERs and ICURs. Missing data will be analysed through Student’s *t* and *χ*^2^ tests for ED severity level, sex, and age; this will allow us to know whether missing data due to dropout are related to chance. Finally, a sensitivity analysis will be carried out to test the robustness of cost-effectiveness and cost-utility results.

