### Objectives and hypotheses

We believe that the implementation of transdiagnostic therapy at the primary level using a stepped-care model would save costs and reduce waiting lists. Mild to moderate cases could be treated in primary care and severe ones could be referred to specialized care for combined and more intensive therapies.

The proposed trial aims to compare, in terms of cost-effectiveness and cost-utility, a brief, transdiagnostic CBT in two different formats, individual and group, with the treatment ordinarily administered in primary care (treatment as usual [TAU]) for mild to moderate EDs (i.e., depressive, anxiety, and somatoform disorders). We expect that:

#### Hypothesis 1

Individual treatment will be generally as effective as group treatment in reducing emotional symptoms and cognitive-emotional regulation biases (i.e., both will show similar post-intervention size effects).

#### Hypothesis 2

The TAU will be the least effective (i.e., with significantly lower post-intervention size effects).

#### Hypothesis 3

The group therapy will return the best results in terms of cost-effectiveness and cost-utility.

#### Hypothesis 4

The TAU will have the least cost-effectiveness and cost-utility ratios.

#### Hypothesis 5

The same results will be found across the follow-up assessments (6 and 12 months after intervention).

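### The economic results are defined only as pairwise ratios of mean differences, so the group versus individual ratio is likely to be unstable in sign and size, and H3 and H4 should not rest on it

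*Protocol article*

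**What the plan says.** All from the protocol article.

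- **Analyses of cost-effectiveness and cost-utility.** The ICER is "the difference in mean costs between interventions divided by the difference in their effectiveness according to the participants’ mean scores", with "one ICER per each comparison between two clusters and per each instrument". The ICUR is "defined as the difference in mean costs divided by the difference in mean QALYs (i.e., one ICUR per each comparison between two clusters". Bootstrapping "will be used to obtain more accurate ICERs and ICURs". A sensitivity analysis is announced without content. The section names no net-benefit measure and no baseline adjustment of costs or QALYs.
- **Objectives and hypotheses.** H1: "Individual treatment will be generally as effective as group treatment in reducing emotional symptoms and cognitive-emotional regulation biases", glossed as "both will show similar post-intervention size effects". H3 expects group therapy to give the best cost-effectiveness and cost-utility. H4 expects TAU to have the lowest such ratios. The Discussion repeats the equal-effect expectation for symptoms and emotion regulation, and makes clear that TAU is expected to come out worst economically.
- **Sample size.** An earlier three-arm trial found differences between the two formats of d = .06 to .27, none significant. Against TAU, d was .54 to .74 for individual and .4 to .63 for group therapy. The plan assumes d = .6 (f = .3), giving 111 participants, raised to 128 for dropout.
- **Data available.** The measures, with a few listed exceptions that do not include the EQ-5D-5L, "will be collected at baseline, immediately after treatment, and 6 and 12 months later (see Table 2". Cost data are collected "from 3 months before inclusion in the study to 12 months after the intervention" (Cost analysis).

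**The concern.** A cost-effectiveness ratio can be read only when its denominator is clearly away from zero. With three arms there are three pairs, and one of them is group versus individual. For that pair the trial's own hypothesis puts the symptom and bias difference close to zero. If H1 is right, the ICERs that should help decide H3 divide by an estimate whose sign is largely chance.

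The sign of the ratio then says little. With effect coded as improvement, a negative ratio arises when an arm is cheaper and better (dominant) and also when it is dearer and worse (dominated). A positive ratio arises when an arm is dearer and better, where a low value is favourable, and also when it is cheaper and worse, where a low value is unfavourable. Bootstrap replicates of such a ratio mix these four situations, so a mean or percentile interval of the replicates has no ordering. Resampling describes the uncertainty; it does not make the ratio more accurate.

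H4 has a related problem. The three ratios belong to group–individual, group–TAU and individual–TAU. None belongs to TAU alone, so there is no set of arm-level ratios in which TAU could rank lowest.

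At stake is the trial's stated aim, the economic comparison of the three arms.

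**Working it through.** **1. The plan's own figure.** A one-way ANOVA with 3 groups, f = .3 and α = .05 (noncentral F, λ = N·f²) gives power .803 at N = 111 and .792 at N = 108. The stated 111 is reproduced, and 1:1:1 allocation gives 111/3 = 37 per arm. The 128 is 111 × 1.15 = 127.65, rounded up. After 15% loss, 128 × .85 = 108.8, about 36 per arm, so 37 is a fair analysed number.

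**2. Precision of the denominator.** In SD units, SE = √(2/n) = √(2/37) = .2325.

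**3. Chance of a wrong-signed denominator.** P = Φ(−d/SE). The last column is the probability that the 95% interval for the effect difference covers zero.

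| Comparison | True d (source) | d/SE | P(wrong sign) | P(95% CI covers 0) |
|---|---|---|---|---|
| Group vs individual | 0 (H1 taken literally) | 0 | .50 (either sign equally likely) | .95 |
| Group vs individual | .06 (Sample size) | .258 | .40 | .94 |
| Group vs individual | .27 (Sample size) | 1.161 | .12 | .79 |
| Versus TAU | .4 (lowest in the earlier three-arm trial) | 1.720 | .04 | .59 |
| Versus TAU | .6 (planning value) | 2.581 | .005 | .27 |

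With no loss at all (128/3 = 42.7 per arm, SE .2165), the values at d = .06 and .27 are .39 and .11.

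**4. What this does to the ratio.** This is an illustration only. Assume a cost difference of −0.5 SD, with independent normal errors of SE .2325 for both cost and effect (1,000,000 draws). The documents give no cost SD or cost difference. The central 95% of the ratio, in cost SDs per effect SD, is:

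- d = 0: about −34 to +35
- d = .06: about −34 to +33
- d = .27: about −19 to +16
- d = .6: about −3.5 to −0.04

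At the planning effect the ratio keeps one sign across that range. At the effects expected between the two formats it does not.

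**5. What baseline adjustment would add.** Adjusting for a baseline value that correlates r with the outcome multiplies the variance of the difference by 1 − r². The documents do not give r, so a range is shown.

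| Assumed r | 1 − r² | 37 per arm acts like 37/(1 − r²) | P(wrong sign), d = .06 | P(wrong sign), d = .27 |
|---|---|---|---|---|
| .3 | .91 | 41 | .39 | .11 |
| .5 | .75 | 49 | .38 | .09 |
| .7 | .51 | 73 | .36 | .05 |

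At d = .06 adjustment hardly changes the picture. At d = .27 and r = .7 the wrong-sign probability falls to .05, but the 95% interval still covers zero with probability .63. Adjustment is worth having for precision; alone it does not stabilise this ratio.

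**The case against.** The definitions are the textbook ones. A journal article may leave covariate adjustment, net benefit and acceptability curves to a fuller plan, and a sensitivity analysis is announced. Only one of three pairs is affected, and the objective is framed mainly against TAU. H4 may be loose English, since the Discussion shows what is meant.

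Much of this stands, and it limits what may be concluded. A reader might infer several stronger points that the documents do not support:

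- **That baseline data are ignored.** The article is silent on adjusting costs and QALYs; it does not exclude adjustment. For scores, the Outcomes section and Analysis of clinical effectiveness assess effectiveness as change from pre-treatment.
- **That pre-inclusion costs are added to the total.** Cost analysis says they are collected and does not say they are summed in.
- **That unadjusted differences are biased.** Under randomisation, chance baseline imbalance costs precision. How large it might be in QALYs cannot be computed, because no utility SD is given.
- **That the trial expects equal QALYs.** H1 and the Discussion speak of symptoms and regulation. For the ICUR, a near-zero denominator is a reasonable extrapolation, no more.
- **That the whole economic analysis fails.** Against TAU at d = .6 the wrong-sign probability is about .005.

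The objection does not remove the core. The article does not merely omit a summary. It fixes the ratio as the result for every pair, including the one where it predicts no difference, and offers bootstrapping as what makes the ratio more accurate. H3 needs that pair, and H4's wording does not match a pairwise definition whatever was intended.

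**Conclusion.** The point holds in limited form. For group versus individual tCBT, the symptom and bias ICERs will probably be unstable in sign and size: the denominator has the wrong sign with probability about .40 at d = .06 and .12 at d = .27, and at d = 0 its sign is a coin toss. Bootstrapping the ratio does not repair this. The same is likely for the ICUR but is not implied by any stated QALY expectation. H4 cannot be tested directly as worded.

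The figures assume 37 per arm, a normal approximation, an unadjusted difference at one time point, and symptom effect sizes from the earlier trial. The ratio ranges also assume a cost difference of −0.5 SD. Comparisons with TAU are largely sound at the planning effect, though less so towards d = .4. No figure stated in the article changes. The lack of a named baseline adjustment is a missed gain in precision, not an error. This should be changed before analysis, but it does not threaten the trial.

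**What to change.** 1. Judge H3 and H4 on incremental net monetary benefit for QALYs over a stated willingness-to-pay range, with bootstrapped intervals and acceptability curves across all three arms together.
2. Reword H4 so that it can be tested, for example that TAU has the lowest expected net benefit of the three arms over that range.
3. Report incremental costs and incremental effects separately for each pair. Give an ICER or ICUR only where the effect difference is clearly non-zero.
4. Describe the bootstrap as a measure of uncertainty.
5. Estimate incremental QALYs adjusted for baseline EQ-5D-5L utility, and incremental costs adjusted for the cost of the 3 months before inclusion. State that this cost is a covariate and not part of the total. Take the score effects from the linear mixed model in Analysis of clinical effectiveness.

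The cost is revised analysis wording and a little programming. All the data are already being collected. If a fuller analysis plan already contains these elements, the article's definitions need only be aligned with it.
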